**Intervention protocol**

Voluntary participants will be assessed for eligibility, collection of demographic data, and completion of a maximal effort 5-minute run test on a 400-m track to determine their individual maximal aerobic speed.

Subsequently, participants will be scheduled for three sessions (once a week) to undergo the intervention under three different conditions, with the order randomized: one without a bandage (CONTROL), one with a tape bandage, and another with KT.

The bandaging will be consistently applied to the dominant leg by a physiotherapist with ten years of clinical experience specializing in ankle and foot injuries in runners, within the Sports Performance Laboratory of the European University of Madrid.

A 10-minute warm-up will be performed based on lower limb mobility exercises, ballistic stretching and running. Subsequently, an assessment of lower limb stability, ankle dorsiflexion mobility, electromyographic activation of the ankle muscles, and jumping ability will be performed, before starting the treadmill protocol.

Following this evaluation, a fatigue protocol will be implemented, involving a 30-minute run at 85% of the maximal aerobic speed on a treadmill. Once completed, an immediate reevaluation will be conducted for all previously administered tests, to collect the same variables as at the beginning of the running protocol.

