**STUDY PROTOCOL – TAPE TRIAL**

**Study design and ethical considerations**

A cross-over, longitudinal, clinical trial with three intervention arms will be conducted in the Sports Performance Laboratory of the European University of Madrid (Spain), adhering to the Helsinki Declaration. Each participant will complete and signed a written consent form before being enrolled in the study.

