**Participants**

The inclusion criteria will be (1) males and females (2) between 18 – 45 years old (3) well-trained, with a weekly training schedule of at least two days and a total of 20 km of running. The exclusion criteria will be determined by the presence of musculoskeletal lower limb or lumbopelvic pathology in the last year.

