**Statistical analysis**

The statistical analysis will be performed with the SPPS software version 29 for Windows. First, data distribution will be assessed with the Shapiro-Wilk test or Kolmogorov-Smirnov test. Then, a one-way ANOVA will be performed to analyze the difference between groups at baseline. Finally, a two-way ANOVA of repeated measures (3 x 2; 3 groups and 2 times of measurement) will be carried out to analyze the difference between groups pre and post treadmill protocol. The investigator who performs the statistical analysis will be blinded. All variables will be analyzed individually, and multiple comparisons will account for using a Bonferroni correction. The significance level will be set at 0.05.

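### Post-run tests are placed after a completed 30-minute run and the ANOVA needs all six values, so one unfinished run would drop a runner from all three conditions

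*Protocol*

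**What the plan says.** All references are to the Protocol.

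- **Study design and ethical considerations:** the trial is "A cross-over, longitudinal, clinical trial with three intervention arms", so each runner is meant to be measured under every condition.
- **Intervention protocol, speed:** this is set individually after "completion of a maximal effort 5-minute run test on a 400-m track to determine their individual maximal aerobic speed".
- **Intervention protocol, sessions:** "participants will be scheduled for three sessions (once a week) to undergo the intervention under three different conditions". Each session has tests, then a fatigue run, "involving a 30-minute run at 85% of the maximal aerobic speed on a treadmill", then tests again.
- **Intervention protocol, second round of tests:** "Once completed, an immediate reevaluation will be conducted for all previously administered tests". The section does not say what happens when a run ends early.
- **Participants:** the minimum training level is "a weekly training schedule of at least two days and a total of 20 km of running".
- **Statistical analysis:** "a two-way ANOVA of repeated measures (3 x 2; 3 groups and 2 times of measurement) will be carried out" to compare the conditions before and after the run. This is the only main analysis named.

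**The concern.** Two choices act together. The only stated route to a post-run value is through the end of the 30-minute run. The named analysis has condition and time both within runner, and in its classical form it cannot use a runner with an empty cell. An unfinished run under one condition would therefore discard the runner's good data from the other two sessions as well.

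Two things are at stake. The first is power, because the number analysed falls faster than the number of failed sessions. The second is selection. Whether a runner finishes is decided after the bandage is on, and the question concerns performance under fatigue. If those who stop are the most fatigued, and if the bandage affects who stops, the completers no longer represent the comparison that was randomised.

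**Working it through.** **Inputs from the Protocol:** 3 sessions per runner, and 3 x 2 = 6 values per runner per outcome. No sample size, effect size or early-stop rate is stated, so there is no planned figure to reproduce.

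**Assumed input:** p, the probability that a session's run ends early and yields no post-run value. The values 5%, 10% and 15% are for illustration.

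**Step 1: runners lost under the complete-case ANOVA.** A runner is kept only if all three runs are finished.

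- Independent stops: loss = 1 - (1 - p)^3.
- Full clustering (a runner who stops once stops every time): loss = p.
- Intermediate case, beta-binomial with an assumed within-runner correlation of 0.5: loss = 1 - (1 - p)(2 - p)(3 - p)/6.

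| p per session | Independent | Correlation 0.5 | Full clustering |
|---|---|---|---|
| 5% | 1 - 0.857 = 14% | 1 - 0.911 = 9% | 5% |
| 10% | 1 - 0.729 = 27% | 1 - 0.827 = 17% | 10% |
| 15% | 1 - 0.614 = 39% | 1 - 0.747 = 25% | 15% |

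For an assumed 20 enrolled, independence leaves 17.1, 14.6 or 12.3 runners. Full clustering leaves 19, 18 or 17.

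**Step 2: does one empty cell matter?** A standard repeated-measures ANOVA routine was given 12 simulated runners with one of their 72 values removed. It refused to fit because the data were unbalanced. The usual way round this is to delete the runner.

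**Step 3: power.** This uses a noncentral F for a three-level within-runner factor at alpha 0.05, with noncentrality n x 3 x f^2/(1 - rho), rho = 0.5 and f from 0.2 to 0.4. Both rho and f are assumed. The sample sizes that give about 80% run from 42 (f = 0.2) down to 12 (f = 0.4). With independent stops and the analysed number rounded down:

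- p = 5%: power 72% to 74%.
- p = 10%: power 60% to 65%.
- p = 15%: power 52% to 57%.

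Clustering softens this. At f = 0.3 the starting number is 20. Full clustering at p = 15% leaves 17, the same number as independence at p = 5%, and power is then about 74%.

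**Step 4: can selection bias the contrast?** In a simulation, each session's change was a runner component (SD 1.5) plus session noise (SD 1.5), with a true tape-minus-control difference of -1.0. A run counted as stopped when that session's change fell below -4, -3 or -2.5. Estimates from runners with all three runs finished were:

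| Effect of tape | Runners lost | Completer estimate |
|---|---|---|
| Same for all | 11%, 24%, 33% | -0.90, -0.84, -0.80 |
| Varies between runners (SD 1.0) | 13%, 27%, 36% | -0.80, -0.69, -0.63 |

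Stopping was built to depend on the outcome, and so on the condition. The result shows that the mechanism works. It does not show that it will operate in this trial.

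**Step 5: after the fix.** With every available session analysed, the loss from early stops is at most p of the post-run values (5%, 10% or 15%), and none if every stopped runner is re-tested.

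**The case against.** - **The wording may only describe sequence.** The section walks through a session in order, and its timing phrase need not mean that a runner who stops early goes unmeasured. This stands: a reader might infer that re-testing is ruled out, but the text is silent on that case. What remains is that site staff have no other instruction.
- **Early stops are not shown to be likely.** The Protocol describes entrants as well trained and sets the speed from each runner's own test. This stands too. The modest entry threshold and a run six times as long as the 5-minute test make stops plausible, but nothing in the document supports a rate.
- **The loss may be smaller than independence suggests.** The same runner repeats the same individual task, so stops should cluster. This is right, and it is why the size is given as a range.
- **A shortfall against the planned size cannot be shown.** A reader might infer that the trial will fall below its calculated number. The Sample size calculation section gives no number and does not say whether losses will be allowed for.
- **Dropping whole runners need not bias a cross-over.** The same people remain in all three conditions. If stopping is unrelated to condition and to response, the cost is power and generalisability only. This stands, and limits the bias claim to a conditional one.
- **The word *groups* and the one-way baseline ANOVA** could suggest that condition is treated as between runners, so that a stop would lose one session only. The cross-over design and the repeated-measures label favour the within-runner reading.
- **Missing-data rules belong in the SAP.** Agreed. Their absence is no part of this point, which rests on when the Protocol takes the measurement and which analysis it names.

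**Conclusion.** The point holds in a conditional form. As written, the timing of the post-run tests and the complete-case ANOVA together mean that one unfinished run would remove a runner from all three conditions. For assumed stop rates of 5%, 10% or 15% per session, between 5% and 14%, 10% and 27%, or 15% and 39% of runners would be lost, depending on how far stops cluster within runners. Power falls accordingly. Bias is possible if stopping depends on the condition or on the runner's response to it.

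The document does not support saying that re-testing is forbidden, that early stops are likely, that the comparison is biased, or that the sample will fall short of plan. The change is still worth making because it costs little and loses almost nothing if every run is completed.

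**What to change.** **Statistical analysis section.** Replace the complete-case ANOVA as the main analysis with a linear mixed model. Use fixed effects for condition, time and condition by time, and random effects for participant and for session within participant. Include every available session under its assigned condition. Report the complete-case ANOVA as a sensitivity analysis. With complete data the two agree closely. With a session lost, the model keeps the runner's other data.

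**Intervention protocol section.** State that a runner who ends the run early and is judged able to be tested is still re-tested at that point. Record the minutes run and the reason for stopping, and report early stops by condition. Both changes are needed, because a mixed model cannot recover a post-run value that was not collected.

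**Cost.** A few sentences and two recorded items per session. Some post-run values will follow a shorter run, possibly much shorter, so the analysis restricted to completed runs should be reported alongside.

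Whether a runner may be tested after stopping, and the run's speed, length and stopping criteria, are left to the investigators.

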**Taping techniques**

***KT Bandage***

In the KT technique, three segments of elastic KT will be employed: two segments fashioned into Y-configurations and one segment in an I-configuration. Initially, the I-configured segment will be affixed longitudinally from the tibial malleolus to the peroneal malleolus, traversing the anterior portion of the ankle. Subsequently, the elongated Y-configured segment will be placed commencing from the lateral facet of the calcaneus extending to the fibular head, enveloping the PL muscle. Thereafter, another shorter Y-configured segment will adhere from the posterior facet of the calcaneus to the base of the first metatarsophalangeal joint, ensuring comprehensive coverage of the targeted anatomical area.

***Tape Bandage***

The ankle taping procedure will be executed utilizing a conventional 38 mm self-adhesive tape, initiating with the application of two anchor straps at a position approximately 10 cm proximal to the malleoli. This will be followed by the strategic placement of two additional straps extending from the medial edge of the anchor strap to the lateral side, with the foot maintained in a neutral position. Subsequently, "figure six" configurations will be crafted, commencing with a strip originating from the medial anchor, passing through the plantar aspect of the foot, and reattaching to the medial anchor. To finalize the taping ankle procedure, the practitioner meticulously will cover all terminal ends and any laxity with adhesive tape, ensuring a secure and uniform application.

**Blinding**

Because of the nature of the intervention, there will be no blinding of the participants or the physiotherapist who performed the taping.

**Statistical analysis**

The statistical analysis will be performed with the SPPS software version 29 for Windows. First, data distribution will be assessed with the Shapiro-Wilk test or Kolmogorov-Smirnov test. Then, a one-way ANOVA will be performed to analyze the difference between groups at baseline. Finally, a two-way ANOVA of repeated measures (3 x 2; 3 groups and 2 times of measurement) will be carried out to analyze the difference between groups pre and post treadmill protocol. The investigator who performs the statistical analysis will be blinded. All variables will be analyzed individually, and multiple comparisons will account for using a Bonferroni correction. The significance level will be set at 0.05.

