**Sample size calculation**

The sample size will be calculated using the G*Power 3.1.9.2 software (G*Power©, University of Dusseldorf, Germany). This analysis will employ a two-tailed hypothesis, an alpha error probability of 0.05, and a beta error of 0.2. A pilot study involving 10 participants will analyze the partial eta squared effect size for the primary outcome, which was the height in the SLDJ between groups and time.

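### The pre-run comparison uses an independent-groups one-way ANOVA on the same participants measured three times, and the 3 x 2 ANOVA does not say that condition is a within-participant factor

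*Protocol*

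**What the plan says.** The Protocol, under Study design and ethical considerations, describes the trial as follows: "A cross-over, longitudinal, clinical trial with three intervention arms". Under Intervention protocol, "participants will be scheduled for three sessions (once a week) to undergo the intervention under three different conditions, with the order randomized". Each person therefore supplies data under CONTROL, tape and KT, both before and after the treadmill run.

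The Statistical analysis section names two tests. For the pre-run data: "Then, a one-way ANOVA will be performed to analyze the difference between groups at baseline". For the pre-to-post comparison: "a two-way ANOVA of repeated measures (3 x 2; 3 groups and 2 times of measurement) will be carried out". Only the second is described as repeated measures. On the level of the tests: "The significance level will be set at 0.05".

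Under Sample size calculation, the primary outcome is single-leg drop jump (SLDJ) height compared across groups and time, which is what the 3 x 2 model tests. The effect size is to come from a pilot of 10 participants. No sample size, standard deviation or within-person correlation is given.

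**The concern.** There are no three groups of people in this trial. A one-way ANOVA takes its error from the spread of participants within each condition, which includes the stable differences between runners. Those differences cancel when each runner is compared with himself or herself, so they do not belong in the error of a comparison between conditions. With positively correlated sessions the test rejects too rarely, and a finding of no pre-run difference means little.

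This affects interpretation. The Protocol does not state outright when the bandage goes on, although Intervention protocol describes the bandaging before the warm-up and pre-run tests. If the bandage is on by then, the comparison measures the immediate effect of taping on balance, dorsiflexion, EMG and jumping. If not, it checks that the three sessions started alike. In both cases a test with too large an error term can give false reassurance.

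The 3 x 2 model raises a smaller question. Calling the three-level factor groups, and reserving the language of measurement for time, is also how a design with one between-subject and one within-subject factor is usually described. An analyst could set the model up that way.

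**Working it through.** **Inputs from the Protocol.** Three conditions per participant and two times per session (Intervention protocol; Statistical analysis); alpha 0.05 (Statistical analysis). There is no stated figure to reproduce.

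**Assumptions.** n = 20; equal variances and equal correlation between any two sessions; within-person correlation ρ of 0.6, 0.8 or 0.9 for pre-run values, and 0 to 0.5 for post-minus-pre changes.

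**Step 1: the error term.** Let σ² be the variance of one pre-run value.
- True variance of a difference between two condition means: 2σ²(1 − ρ)/n.
- Variance implied by the one-way ANOVA: 2σ²/n.
- Ratio of standard errors: 1/√(1 − ρ). For ρ = 0.6, 0.8 and 0.9 this is 1/√0.4 = 1.6, 1/√0.2 = 2.2 and 1/√0.1 = 3.2.

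**Step 2: effect on the pre-run test.** For n = 20 the one-way ANOVA refers F to 2 and 3(n − 1) = 57 degrees of freedom, with the within-condition mean square as error. The within-participant test uses 2 and 2(n − 1) = 38, with the participant-by-condition mean square as error. Simulated rejection rates with true means 0, 0.2 and 0.4 SD:

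| ρ | One-way, type I error | One-way, power | Within-participant, power |
|---|---|---|---|
| 0.6 | 0.2% or less | about 6% | 39% |
| 0.8 | 0.2% or less | about 2% | 68% |
| 0.9 | 0.2% or less | about 0.6% | 94% |

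The within-participant test holds its type I error at about 5%. With evenly spaced means and a larger range, the one-way ANOVA recovers: power is about 57% at a largest difference of 0.8 SD, and 85% to 92% at 1.0 SD.

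**Step 3: the 3 x 2 model.** With two times, the condition-by-time test equals a comparison of the three conditions on the post-minus-pre change. If both factors are within participant, the error term is right and type I error stays near 5%. If condition is entered as between-subject, the fault of Step 1 returns, now governed by the correlation of changes across sessions. With a largest difference of 0.8 SD of the change score:

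| Correlation of changes | Power, condition between | Power, condition within |
|---|---|---|
| 0 | no loss | no loss |
| 0.1 | about 58% | 63% |
| 0.3 | about 58% | 74% |
| 0.5 | about 57% | 88% |

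**The case against.** The strongest reply concerns the main analysis. A reader might infer that the 3 x 2 ANOVA also treats the sessions as independent, so that the cross-over's precision is lost for the primary outcome. The Protocol does not support that. It labels this model as repeated measures, and in a design where everyone receives all three conditions the ordinary reading has both factors within participant. Nowhere does it say that condition is between-subject. The word groups is loose, and the Sample size calculation section uses it in the same loose way. What remains is an ambiguity, and the second table applies only if it is resolved the wrong way.

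Two further inferences also fail. One is that the one-way test will report no difference whatever the bandage does; Step 2 shows that it often detects 0.8 to 1.0 SD. The other is that the plan discards anyone lacking one of the six measurements. That would apply to a model with all six in one participant record, which is the valid reading, so it cannot be charged together with the between-subject error. Handling of missing data may also be set out in an SAP that is not shown.

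It is also fair to say that the one-way error is conservative, so it does not create false positives, and that no section makes the main test depend on the pre-run result. Both limit the severity. Neither makes the one-way test right: the next sentence of the same section specifies repeated measures where that is meant, and the pre-run test carries no such label.

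**Conclusion.** The one-way ANOVA is wrong as written. It is an independent-groups test applied to three measurements of the same people, and it is too conservative for any positive correlation between sessions. The direction follows from the design. The size rests on the assumed n, correlations and effects, because the Protocol gives none: small differences of up to 0.4 SD would nearly always be missed, while large ones often would not.

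For the 3 x 2 ANOVA the conclusion is narrower. It is valid with both factors within participant, and its wording should exclude the alternative. A loss of power for SLDJ height is not shown; it would arise only if condition were entered as between-subject and changes were correlated across sessions.

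This should be fixed, but it does not threaten the main result: the clear error sits in a preliminary comparison and does not inflate false positives.

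**What to change.** In the Statistical analysis section:

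1. Replace the one-way ANOVA with a repeated-measures ANOVA on condition for the pre-run values, or take the pre-run condition contrasts from the main model.
2. Replace the reference to three groups with: *condition (CONTROL, tape, KT) and time (pre, post), both within-participant factors*.

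A linear mixed model with a participant term would be an acceptable alternative but is not required. The change is to wording only; the software and data stay the same.

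### Bonferroni for the three condition comparisons is valid but needlessly conservative, and the planned 80% power belongs to the overall test, not to any pair

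*Protocol*

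**What the plan says.** Under Intervention protocol, each participant is scheduled "to undergo the intervention under three different conditions, with the order randomized": no bandage, tape and KT. Three conditions give three pairs.

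Under Sample size calculation, the stated settings are "an alpha error probability of 0.05, and a beta error of 0.2", two-tailed. The effect to be powered comes from a pilot: "A pilot study involving 10 participants will analyze the partial eta squared effect size for the primary outcome". That outcome is single-leg drop jump (SLDJ) height, and the effect is described across groups and time. Partial eta squared across three conditions is an omnibus measure. No N, effect size or standard deviation is given, and no power is stated for any pair.

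Under Statistical analysis, "a two-way ANOVA of repeated measures (3 x 2; 3 groups and 2 times of measurement) will be carried out". Each variable is then analysed on its own, "multiple comparisons will account for using a Bonferroni correction", and the significance level is 0.05. The section does not list the comparisons in the Bonferroni family, and it does not say whether pairs are tested only after a significant F test.

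**The concern.** A reader of this trial will want to know which of tape, KT and no bandage differs, and the pairwise comparisons answer that. The study is sized at 0.05 for an overall effect, while each pair is judged at 0.0167. Nothing in the sample size section allows for the stricter level. Two things follow.

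- Someone reading the 80% as the chance of identifying an effective bandage would be too optimistic.
- With exactly three conditions there are procedures with the same family-wise error guarantee that reject more often than Bonferroni, so some of the shortfall can be avoided.

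The protocol itself fixes both the sizing alpha and the Bonferroni rule, so the point concerns what is stated and not detail left to a later analysis plan.

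**Working it through.** **Inputs from the protocol.** Two-sided alpha 0.05; power 0.80; three within-participant conditions; Bonferroni. Because no N or effect is stated, there is no figure of the plan to reproduce. The effect is instead set so that the stated 80% holds, and the power for a pair is read off.

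**Assumptions.** n = 12, 20 or 30; normal errors; sphericity; the condition-by-time interaction treated as a one-way repeated-measures comparison of pre-post changes; paired t tests with n − 1 degrees of freedom. Effects are in units of the error SD of the changes.

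**Step 1: effect that gives the omnibus test 80%.** Noncentral F with 2 and 2(n − 1) degrees of freedom: λ = 11.08 (n = 12), 10.44 (n = 20), 10.15 (n = 30).

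**Step 2: what that means for a pair, n = 20.**
- One condition differs by d from two equal ones: λ = n × 2d²/3, so d = √(10.44 × 3/40) = 0.885. The paired t test has noncentrality d√(n/2) = 0.885 × √10 = 2.80.
- Equally spaced conditions, step δ: λ = n × 2δ², so δ = √(10.44/40) = 0.511. Noncentrality is 0.511 × √10 = 1.62 for an adjacent pair and twice that, 3.23, for the extreme pair.

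**Step 3: power per true pair**, simulated with 100,000 trials per scenario. The closed test is a Greenhouse-Geisser-corrected F test at 0.05, then each pair at 0.05. Ranges show the spread between independent runs.

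| Pattern | n | Pair | Bonferroni | Holm | Closed test |
|---|---|---|---|---|---|
| One differs | 12 | each true pair | 54-55% | 58-59% | 68-69% |
| One differs | 20 | each true pair | 58% | 61-62% | 70% |
| One differs | 30 | each true pair | 59% | 63% | 71% |
| Equally spaced | 20 | extreme | 72-73% | 73-74% | 78% |
| Equally spaced | 20 | adjacent | 18-19% | 24% | 32% |

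**Step 4: a different sizing.** If N were set for 80% on one pair at 0.05, the normal approximation gives Bonferroni power Φ(1.960 + 0.842 − 2.394) = Φ(0.408) = 66%. With t tests at n = 12 to 30 it is 61-64%, against about 76% for the closed test without the Greenhouse-Geisser correction.

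**Step 5: why unadjusted pairs can be valid after a gate.** If all three conditions are equal, the F test at 0.05 limits the error. If they are not all equal, at most one pair can be equal, because two equal pairs force the third. That single true null hypothesis is tested at 0.05. In simulation at n = 20, the family-wise error of the corrected closed test was 4.6% with all conditions equal and 4.9% for the one remaining equal pair. The gate needs the sphericity correction: with correlations of 0.9, 0.6 and 0.6 between conditions, the uncorrected F test ran at 6.7% and the corrected one at 4.8%.

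**Step 6: where that argument fails.** It requires the gate and the pairs to concern the same quantity. Suppose the conditions differ before the run but not after it, and a significant interaction is followed by unadjusted pairs of post-run values. All three pairs are then null. At n = 20, family-wise error is about 9% when the gate has 77% power and about 12% when it has nearly 100%.

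**The case against.** Bonferroni is a valid and conventional choice, and choosing among valid procedures is partly preference. This stands: no error rate is inflated and the protocol does not contradict itself.

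A reader might infer that the plan delivers less than the 80% it claims. The protocol does not support that. Its 80% is tied to partial eta squared across groups and time, and no power is claimed for a pair.

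A reader might also infer that every true difference would be found only slightly more than half the time. That holds for one assumed pattern. With equally spaced conditions, Bonferroni finds the extreme pair about 73% of the time and each adjacent pair about 18%. None of these is a property that the protocol fixes.

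A third tempting inference is that the correction is redundant and can simply be dropped after the ANOVA. The protocol does not say that the F test gates the pairs, so Bonferroni may be the only protection. In a 3 × 2 design the pairs could be run on change, on post-run values or on averages over time. Unadjusted pairs on post-run values after an interaction gate can reach 9-12% family-wise error, which Bonferroni prevents. Bonferroni also comes with simple simultaneous confidence intervals, which the alternatives do not.

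What survives is narrower. Holm needs no gate and no sphericity, and rejects at least whatever Bonferroni rejects, so the test can be improved whatever N or pattern applies.

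**Conclusion.** The point holds as a modest efficiency improvement together with a clarification of what the 80% means. On the natural reading of three comparisons per outcome, with the omnibus test at 80% power, sphericity, n = 12 to 30 and one condition differing, replacing Bonferroni gains about 4 percentage points per true pair with Holm and about 12 to 14 with a closed test. With equally spaced conditions at n = 20, the closed test gains about 5 points for the extreme pair and 14 for each adjacent pair; Holm gains about 1 and 6. In every one of these scenarios the power for a single pair stays below 80% even with the better procedure, so the sample size statement needs its qualification either way. The three-comparison family is inferred from the design and the variable-by-variable analysis; it is not stated.

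**What to change.** **Statistical analysis.** Replace Bonferroni for the three condition comparisons within an outcome with Holm, and name the three comparisons as the family. This is the simplest change and does not depend on how the ANOVA turns out.

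Alternatively, specify a closed test with gate and pairs on the same quantity, for example: *If the Greenhouse-Geisser-corrected condition-by-time interaction is significant at 0.05, the three paired comparisons of pre-post change between conditions are each tested at 0.05. Comparisons on any other quantity, such as post-run values alone, use Holm or Bonferroni.*

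**Sample size calculation.** State that the 80% refers to the omnibus effect and that power for a single pair is lower. N is still to be calculated, so this can inform it. For the one-condition-differs effect that gives the omnibus test 80% at n = 20, a single pair would need n = 30 to reach 80% at 0.0167, or n = 23 at 0.05.

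**Cost.** A few sentences and no new data. Simple simultaneous confidence intervals are lost. With the closed test, no pair can be declared unless the interaction is significant.
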